### Aims 2 and 3: CD4 Point-of-Care and Peer Navigation

#### Aims 2 and 3 Design

Participants diagnosed with prevalent or incident HIV infection during participation in Aim 1 of the study are offered CD4 POC to assess whether this technology can increase the likelihood that HIV-infected MSM and TW are successfully staged for HIV disease and engaged in care (Aim 2). All persons who accept CD4 POC testing are offered peer navigation and viral load testing in the final stage (Aim 3). Treatment adherence and clinical outcomes, including the proportion of MSM and TW participants who achieve successful viral suppression, is assessed by nonrandomized comparison of participants who accept and decline peer navigation support. Participants of Aims 2 and 3 follow the same procedures; thus, the following section jointly describes the methodology for Aims 2 and 3.

#### Aims 2 and 3 Recruitment

Participants who test positive during Aim 1 or who report a previous diagnosis of HIV infection are offered enrollment by the study team into Aims 2 and 3. Separate consent forms are provided for each of these aims. Specifically, the consent form for Aim 2 requests consent to participate in CD4 POC testing, and the consent form for Aim 3 will request consent for participation in peer navigation.

#### Aims 2 and 3 Study Sample

Inclusion criteria for Aims 2 and 3 are assigned male gender at birth, aged 18 years or older, reports having had any type of sex with another man in the past 12 months, is mentally sound and capable of providing consent to participate, speaks Myanmar, current resident of the greater Yangon area, diagnosed with HIV infection, not currently engaged in any treatment or care programs, and has provided informed consent to participate in the study. Participants will be excluded from Aims 2 and 3 if they report that they are already linked into an HIV treatment or care program or have tested negative for HIV infection.

The overall study sample size estimate was driven by the numbers needed for the feasibility and acceptability studies of CD4 POC testing, viral load, and peer navigation, with a target of 54 participants in CD4 POC testing to assess key parameters. Assuming a 10% decline in participation for peer navigation and viral load testing, our target sample for viral load and peer navigation is 49 participants. As data analysis and monitoring are ongoing during data collection, RDS can be extended for additional recruitment should additional recruitment be required to reach targets in Aims 2 or 3. Further, if necessary to reach our desired Aim 2 sample size, additional MSM and TW who are newly HIV-diagnosed can be recruited from partnering organizations for this phase.

#### Aim 2 CD4 Point-of-Care

CD4 POC testing capacity is available at the study site. Given the need for CD4 POC testing, there is no randomization of participants during this phase of research. We use the BD FACSPresto Near Patient CD4 Counter (BD Biosciences) system for POC CD4, which is currently available but in limited use in Myanmar. This system uses the BD FACSPresto cartridge, which contains desiccated reagents that eliminate requirements for a cold chain and cold storage and is well-suited to rural areas and settings with unstable power. The BD FACSPresto Near Patient CD4 Counter system was selected given its availability in Myanmar and limited use by local nongovernmental organizations in Myanmar to provide free CD4 POC services to key populations who have been diagnosed with HIV infection. The system is portable and can provide easily read CD4 outputs within 20 minutes, while patients wait to receive their results. The BD FACSPresto machine contains a built-in training module along with a detailed manual for easy training and operation. In addition to this, laboratory staff attended a training provided by Yee Shin Co Ltd, the Yangon-based regional distributer of the machine and cartridges. Yee Shin Co Ltd is also available to the staff for troubleshooting and other maintenance services as needed. Prequalified by WHO, the BD FACSPresto Near Patient CD4 Counter system has demonstrated reliability and accuracy when used in resource-limited settings [45-47]. This innovation can reduce continuum losses through immediate provision of results, post-CD4 stage counseling, and access to treatment for those who meet treatment criteria on the day of testing. Persons with very low CD4s can thereby be immediately engaged with peer navigators (Aim 3) to seek ART access.

#### Aim 3 Peer Navigation

If successful, increasing HIV status awareness through HIVST and POC CD4 will identify a significant number of persons in need of health care and ART. All Aim 2 participants are offered enrollment in Aim 3, which intends to address barriers to HIV care and ART adherence by comparing those who opt into peer navigation to those who decline.

Peer navigation is offered to all participants on the account of high rates of existing AIDS-related morbidity and mortality among MSM and TW populations living with HIV in Myanmar. For this phase of the project and given the severity of clinical needs, we will not conduct a randomized assessment of peer navigation. Consequently, we measure actual numbers of persons who successfully start on ART, comparing those who opt into peer navigation to those who decline. We treat this aim as an observational study, with peer navigation assistance as the exposure of interest and ART uptake as the outcome. All eligible participants are offered peer navigation with approximately 8 participants assigned to each peer navigator.

Trained peer navigators follow and support all clinically staged participants who have accepted navigation support for 12 months. Peer navigators offer focused training on the importance of CD4 and viral load monitoring, self-care when living with HIV, and methods to prevent HIV transmission. Participants are given contact information for their assigned peer navigator and are encouraged to reach out to them for assistance navigating the Myanmar health system. The role of the peer navigator is to provide support and information to HIV-positive MSM and TW who are seeking HIV treatment and care in the Myanmar. In order to maintain confidentiality in this peer relationship, the questionnaire administration and appointment reminders are the responsibility of office staff.

Peer navigators are selected from the MSM and TW population by Alliance and partner CBOs. Ideally, peer navigators will have prior experience working in HIV prevention or other outreach, but this is not required. Peer navigators undergo an intensive training on topics of MSM and TW health, HIV prevention and care, disclosure of HIV status and issues of social support, and other related topics. Training will build on past training used locally as well as in Malawi and South Africa and incorporate key aspects from the Fenway Guide and other validated MSM training materials [48,49]. Local CBOs and MSM and TW participants also provide input to trainings to ensure contextual relevance. Peer navigators are provided with condoms and lubricants for distribution as well as informational materials on where specific (nonstigmatizing) services can be obtained. Peer navigators are overseen by the research coordinator and report on a weekly basis for debriefing. The research coordinator occasionally monitors participant meetings to ensure fidelity to the curriculum and adherence to the study protocol.

#### Aims 2 and 3 Data Collection

Upon determination of eligibility and verbal confirmation of informed consent, participants complete a structured 20-minute interviewer-administered questionnaire. Participants are then asked to return to participate in surveys conducted at 6 and 12 months. Surveys assess the primary outcome and initiation of ART as well as ART adherence (among those successfully initiated) and other clinical outcomes, including viral suppression, as measured by HIV viral load assessment at 0, 6, and 12 months. This questionnaire is used to assess the strength of peer navigation in improving access and uptake of viral load by MSM and TW living with HIV in care. Peer navigation implementation data (eg, number of meetings per participant, types of support provided) along with participant perceptions will be collected to understand the benefits and challenges of peer navigation and note opportunities for improvement. Incentives are distributed at the conclusion of each follow-up survey. An electronic data entry and tracking system has been developed for this study and allows for registration, screening, survey data collection, data entry of laboratory results, and participant tracking through a secure, Health Insurance Portability and Accountability Act–compliant site. This system is used throughout all phases of the study (Figures 4 and 5).

**Figure 4 figure4:**
[figure not shown]
Participant tracking system (English).

**Figure 5 figure5:**
[figure not shown]
Participant tracking system (Burmese).

#### Aims 2 and 3 Analytical Approach

The primary hypothesis for Aim 2 is that a higher proportion of MSM and TW living with HIV who accept CD4 POC testing will be successfully staged. The primary hypothesis for Aim 3 is that HIV-positive persons who accept peer navigators will have a higher likelihood of achieving ART treatment access than those who decline peer navigation. Aims 2 and 3 are analyzed as observational studies, with CD4 POC testing and peer navigation assistance as the exposures of interest and ART uptake and viral suppression as the outcomes. Specifically, the primary outcomes of interest follow the HIV care continuum and include the actual numbers of persons who accept CD4 staging, are linked to treatment, successfully initiate ART, accept viral load testing and peer navigation, reach viral suppression, and are lost to follow-up.

We conduct longitudinal analyses to measure the associations between these innovations and impact outcomes, including time to CD4 staging, receipt of CD4 results, time to engagement in HIV care and treatment for those eligible, barriers and facilitators to completing CD4 staging, perceived and experienced stigma in health care settings, and uptake of treatment referrals. Regression analysis controls for potential confounding by participant demographics and behaviors. Additional analyses related to peer navigation assess frequency of peer navigator meetings, types of discussions and HIV prevention materials provided, and associated changes in ART adherence and viral load testing. Statistical analysis to achieve Aims 2 and 3 will be conducted using multilevel logistic regression to allow for exposure to peer navigation to vary by time. This will be implemented using regression models specified for proportions in Stata 14 (StataCorp LLC). Longitudinal analysis compares time to CD4 POC and ART (among those eligible) for participants testing positive for HIV infection, controlling for other potential confounders.

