**Methods:**

To assess the effect of HIVST, we will implement a randomized trial in which MSM and TW adults in the greater Yangon metropolitan area who are HIV uninfected will be recruited via RDS (N=366). Participants will complete a baseline socio-behavioral survey and will be randomized to standard, voluntary counseling and testing (VCT) or to HIVST. Biologic specimens will be collected during this baseline visit for confirmatory testing using dried blood spots. Participants will be asked to return to the study office to complete a second study visit in which they will report their HIV test result and answer questions on the acceptability of the assigned testing method. Aim 1 participants with confirmed HIV infection and who are not engaged in care (N=49) will be offered direct enrollment into Aims 2 and 3, which include immediate CD4 POC and the option for peer navigation, respectively. Aims 2 and 3 participants will be prospectively followed for 12 months with data collection including interviewer-administered sociobehavioral survey, CD4 POC, and viral load testing occurring biannually. Participants who accept peer navigation will be compared to those who decline peer navigation. Analyses will estimate the impact of CD4 POC on engagement in care and the impact of peer navigation on ART adherence and viral load.

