#### Aim 1 Follow-Up

All participants are scheduled for a second visit 2 to 3 weeks after the primary visit. During this visit (visit 2), self-reported VCT and HIVST results are ascertained. Analysis of DBS specimens is conducted between visit 1 and 2 to serve as confirmatory testing of results identified through clinic-based VCT or HIVST. Special effort are made to recontact, counsel, and provide appropriate referrals for participants who do not return for the follow-up visit but who are identified with HIV infection during analysis of DBS. Participants found to be preliminarily HIV-negative are given posttest counseling, which includes an explanation of the test result, advice on risk reduction, and the provision of condoms, lubricant, and referrals. These participants are advised to seek HIV testing again in 3 months and are provided with contact information for local nongovernmental organizations who provide HIV testing and care services to MSM and TW. Participants confirmed HIV infected are given posttest counseling and offered enrollment in Aim 2 to conduct immediate CD4 POC staging. Participants who decline enrollment in Aim 2 are provided with referrals for standard CD4 testing as well as treatment and care services. Participants with discordant DBS and self-reported HIVST or VCT results are asked to provide an additional blood sample for confirmation by Western blot.

All participants are asked to complete a structured, 30-minute interviewer-administered questionnaire during visit 2 that serves to evaluate uptake and acceptability of clinic-based or HIVST methods. Participants also receive secondary reimbursement for recruitment of peers at the second visit, which is a standard practice of RDS and will incentivize this follow-up visit.

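### Aim 2 states a higher-proportion hypothesis with no comparator: staging is near 100% by construction, and no effect of CD4 point-of-care on later outcomes can be estimated

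*Protocol article*

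**What the plan says.** The Aims 2 and 3 Analytical Approach gives the Aim 2 primary hypothesis as "a higher proportion of MSM and TW living with HIV who accept CD4 POC testing will be successfully staged". The sentence ends there. The Aim 3 hypothesis beside it does name its comparator: acceptors of navigation "will have a higher likelihood of achieving ART treatment access than those who decline peer navigation". The same section then lists CD4 point-of-care (POC) testing, together with peer navigation, as an exposure of interest, with ART uptake and viral suppression as outcomes.

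The design sections describe who receives the test:

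- Aim 2 CD4 Point-of-Care: "Given the need for CD4 POC testing, there is no randomization of participants during this phase of research". The device "can provide easily read CD4 outputs within 20 minutes" while the patient waits.
- Aims 2 and 3 Recruitment: "the consent form for Aim 2 requests consent to participate in CD4 POC testing".
- Aim 1 Follow-Up: "Participants who decline enrollment in Aim 2 are provided with referrals for standard CD4 testing as well as treatment and care services".
- Aims 2 and 3 Design: those who accept CD4 POC go on to the offer of peer navigation and viral load testing.
- Aims 2 and 3 Study Sample: the target is 54 participants in CD4 POC testing, set for feasibility and acceptability purposes. No number is given for an untested group.

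The claims go further than this. The Abstract (Methods) says "Analyses will estimate the impact of CD4 POC on engagement in care". Aims 2 and 3 Design says the aim is to find out whether the technology raises the chance of staging and engagement. The Discussion says participants are followed to determine its impact on ART initiation and virologic suppression.

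**The concern.** A hypothesis of a higher proportion needs a second proportion, and none is named. Two separate problems follow.

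For staging, the hypothesis is about people who have agreed to a test whose result is the outcome. It will appear confirmed whatever CD4 POC does for continuity of care.

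For linkage, ART uptake and suppression, the outcome is distinct from the exposure, but everyone described as followed has had CD4 POC. A reader of the final report could take high staging or good ART uptake as evidence that on-site CD4 testing works, when the data cannot show what would have happened without it.

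**Working it through.** **The plan's own figures.** The Aim 1 Study Sample section takes 366 participants and 15% HIV prevalence: 366 × 0.15 = 54.9, stated as 54. The Aims 2 and 3 Study Sample section then takes a 10% decline for navigation and viral load: 54 × 0.9 = 48.6, stated as 49. Both reproduce within rounding. All 54 are in CD4 POC testing, so the planned exposed group is 54 and the described, followed unexposed group is 0.

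**Staging.** I assume that being staged means obtaining a CD4 result at the visit; the article does not define it further. With x = n = 54, the exact (Clopper-Pearson) 95% lower limit is 0.025^(1/n):

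0.025^(1/54) = exp(−3.689/54) = exp(−0.0683) = 0.934, so the interval is 93.4% to 100%.

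The article gives no rate of failed or invalid readings. If one or two tests failed:

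| Staged / accepted | Estimate | Exact 95% CI |
|---|---|---|
| 54/54 | 100% | 93.4% to 100% |
| 53/54 | 98.1% | 90.1% to 99.95% |
| 52/54 | 96.3% | 87.3% to 99.5% |

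These results describe how reliably the device yields a reading among people who agreed to it. None bears on a higher proportion, because no second proportion exists.

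**Linkage, ART uptake, suppression.** A risk difference, odds ratio or hazard ratio for CD4 POC needs outcomes at two levels of exposure. With 54 at one level and 0 at the other, none is defined. In a regression, an indicator that equals 1 for every participant cannot be separated from the intercept (or, in a proportional hazards model, from the baseline hazard). A within-person contrast is not available either: the Abstract says CD4 POC is repeated twice a year during follow-up, and only peer navigation is said to vary over time in the multilevel model.

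**Could decliners serve as the comparator?** No decline rate for CD4 POC is given, so the splits below are assumptions. They also suppose that decliners are followed for the outcome, which is not described. Power is for a Fisher exact test at .05, two-sided, total 54:

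| Acceptors vs decliners | 75% vs 60% | 90% vs 50% |
|---|---|---|
| 49 vs 5 | 9% | 50% |
| 43 vs 11 | 13% | 79% |
| 27 vs 27 | 15% | 87% |

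Only a very large difference would be detectable, and the groups would be self-selected. For staging, accepting the test would still almost equal the outcome.

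**The case against.** The best defence is that Aim 2 is already largely descriptive. The sample was sized for feasibility and acceptability. The Analytical Approach spells out the primary outcomes as counts along the care continuum, including the number who accept staging, which implies a base of people offered the test. Aim 2 is openly nonrandomized, and a condensed article leaves detail to other documents. All of this stands, and it makes the remedy easy. It does not rescue the hypothesis sentence or the impact claims: the missing comparator is a matter of design, and no later analysis plan can create one.

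Three stronger readings are tempting and are not supported:

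- *That exposure and outcome coincide throughout Aim 2, so nothing in it can be estimated.* They coincide only for staging. Linkage, ART initiation and suppression are distinct events, and their proportions and times can be estimated in the followed group.
- *That the specified regression contains a constant CD4 POC term.* The article calls CD4 POC an exposure of interest, but the one model it specifies, a multilevel logistic regression, is described in terms of peer navigation varying over time. In the longitudinal comparison, time to CD4 POC is an outcome among people testing positive. What cannot be delivered is the stated exposure contrast.
- *That decliners contribute no data.* Those coming from Aim 1 have the visit 1 questionnaire, and all participants are asked to complete one at visit 2. What is not described is any later follow-up of them for care or ART outcomes.

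**Conclusion.** The point holds. The Aim 2 primary hypothesis has no comparator. For staging, the result is fixed near 100% by the design: 54/54 would give 93.4% to 100%. For linkage, ART uptake and suppression, no effect or association of CD4 POC can be estimated, because the described follow-up has 54 exposed and no unexposed participants, although the Abstract, Aims 2 and 3 Design, the Analytical Approach and the Discussion all promise one.

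This rests on two assumptions: that staging means getting the on-site CD4 result, and that no historical, external or followed untested group exists beyond what the article describes. Acceptance, on-site staging and the later cascade steps remain valid as descriptive estimates.

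**What to change.** 1. Restate Aim 2 as a single-group descriptive cascade, in line with the feasibility purpose in the Aims 2 and 3 Study Sample section and the outcome counts in the Analytical Approach.
2. Report acceptance and on-site staging with exact 95% CIs, with all confirmed HIV-positive people who are eligible and offered CD4 POC as the denominator, not acceptors alone.
3. Report linkage, ART initiation and suppression as proportions and times among those enrolled and followed. Extending these to decliners would need follow-up that is not described, and counting decliners as not engaged would bias the result.
4. In the Analytical Approach, replace the higher-proportion hypothesis and remove CD4 POC as an exposure of interest. In the Abstract, Aims 2 and 3 Design and the Discussion, remove the claims to estimate its impact or to show that it increases staging or engagement.
5. The alternative to step 4 is to name a followed or external comparator. The Results section reports that ART eligibility changed while the study was under way, so an external comparator would have to match on that.

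Steps 1, 3 and 4 change wording only. Step 2 needs a record of everyone offered the test; the article mentions a registration, screening and tracking system but does not say that offers are logged, so this should be checked. The real cost is that Aim 2 will support no comparative conclusion about CD4 POC.

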#### Human Subjects Considerations

Discussion of HIV and sexuality is inherently sensitive in nature. As such, all study activities are conducted with emphasis on confidentiality and privacy of participants. The study office provides the participants with a safe environment free from outward harassment or discrimination. Our collaboration with the International HIV/AIDS Alliance Myanmar and local CBOs serving the MSM and TW populations ensures that all activities are sensitive to stigma and other challenges faced by MSM and TW and designed interventions are acceptable to the population. The surveys and data collection are conducted in a private room located in the study offices. Study staff members are required to complete human subjects training and provide their certificates of training prior to conducting human subjects research. All study activities are conducted in private with individual participants; no individual other than the interviewer or laboratory technician is permitted in the room at the time of data collection. During data collection, the participant has the right to refuse to answer any questions he or she is not comfortable answering to protect privacy.

Trained Alliance staff working on this project obtain informed consent from participants but allow participants to leave a mark in lieu of their signed name. All consent processes use a Myanmar language consent script, approved by Johns Hopkins School of Public Health Institutional Review Board and the local ethical review board. During the consent process, the staff member explains the study in detail, outlining the purpose, sequence of events, rights, potential risks and benefits to participants, and eligibility criteria. This information, along with a local study phone number that can be called with questions or concerns, is available on a paper version of the approved version of consent script. Study staff read aloud the consent form and will allow participants to ask any questions at any time prior to requesting consent for participation in the study. The consent process, along with surveys and biologic specimen collection, will be conducted in private offices to maintain participant confidentiality and privacy.

Study staff keep confidential phone numbers and first names of potential participants for scheduling purposes only. One hard copy of the contact list is stored in a locked cabinet and an electronic version is saved in the electronic tracking system, separate from study data. Only staff members tasked with scheduling participants have access to the electronic list, by permission of the in-country principal investigator. The staff are instructed not to leave any voice or text messages with participants, to verify the identity of the individual, and to not mention any potentially stigmatizing behavior or HIV status during the phone conversations. When the study is mentioned over the phone or while reminding participants of an appointment, it is referred to as a health and wellness project.

Unique identifiers will be used to link study data and are constructed for all participants using information known only to the participant; these will be created to link all surveys, specimens, and laboratory results. The code is formulated from questions that are easily answered, reproducible, culturally appropriate, individually unique, and that MSM and TW will be comfortable answering. The unique identifier is an 8-digit reproducible alphanumerical code developed using the using the first 2 letters of the participant’s last name, the first 2 letters of the participant’s first name, the first 2 letters of the participant’s father’s first name, and last 2 digits of the participant’s birth year. Burmese names are Romanized to English letters based on a transliterated chart of the Myanmar alphabet for purposes of creating a unique ID. During the process of creating the unique ID code with the participant, the study team member indicates that the participant only needs to respond with the appropriate numbers or letters to the question and do not need to give the full response (eg, participant only needs to provide the first letter of the city where he or she currently lives rather than state the full name of the city). Doing so provides an additional layer of privacy for the participants. This unique identifier can be recreated throughout the study and will facilitate linking study participants with biological results while maintaining anonymity. This process has been successfully used in past research studies conducted by this study team [39,50].

All surveys are interviewer-administered and collected using secure, computer-based systems. Anonymous, paper-based surveys are used only as back-up to the computer-based systems. Any anonymous, paper-based data collection forms are secured in a locked cabinet in the project offices. Data entry will take place at the study office, where study data are maintained on designated password-protected computers. Electronic transfer from the study office to JHU occurs only through encrypted files. The JHU principal investigator (CB) and in-country principal investigator (SN) control access to the data. Only relevant study staff who have completed ethical training and have permission from the principal investigator have access to the data.

Following completion of study activities, eligible participants receive 9000 kyat (about US $7) at visit 1 as incentive and reimbursement of travel costs to the project office. Participants who are ineligible at visit 1 also receive 1000 kyat (about US $0.80) for travel expenses. Participants are provided with another 5000 kyat (US $4) at visit 2 for travel expenses as well as an additional 1000 kyat (about US $0.80) for each RDS recruitee who is eligible and participates in the study (maximum of 3 recruitees). These incentive amounts are consistent with other RDS studies implemented in Myanmar and are determined to encourage recruitment without unduly coercing participation [51]. For eligible participants, subsequent visits at 6 and 12 months upon enrollment into Aims 2 and 3 include 10,000 kyat (about US $8) as incentive and to cover travel expenses.

